## **7. RECRUITMENT RATES AND MILESTONES**

Figure 1 shows the projected recruitment of centres and participants, and projected number of men to be approached. Five centres will be established relatively early in the project as an internal pilot followed by roll out to the others over the subsequent months.

An internal pilot is included, primarily designed to verify that recruitment is possible. We will make a decision about feasibility at around month 15 when 82 centre months have been accrued and approximately 43 participants randomised. We anticipate that

this should include 'steady state' data from the five selected pilot centres and initial data from up to 10 other centres more recently set up. This rule will try to statistically assess the accumulating recruitment to see if it is consistent with the required rate to recruit on time and budget to the full trial. It would take the form of 'If recruitment is at least 37 of the anticipated 43, continue unchanged to full study; if between 26 and 36, then consider modifying the design; if 25 or less, consider that the trial is not feasible'. If the trial progressed as planned we would anticipate having 117 randomised participants by month 24, 281 patients by month 36 and the remaining 79 patients by month 42, making a total of 360 participants.

### Extension to recruitment

Due to the slower than anticipated recruitment, a 9 month extension has been approved by the TSC and DMC oversight groups, and Funder (May 2017). Based on a conservative estimate of the recruitment trend, 9 randomised participants per month, for an additional 9 months will result in achieving target recruitment (Figure 1).

**Figure 1 Site accrual and recruitment projections**

[figure not shown]

**Figure 2: Gantt Chart**

[figure not shown]

The funding for the trial started on 1 September 2013 and the duration is 82 months. The Gantt Chart (Figure 2) illustrates the main milestones: pre-funding: multicentre research ethics and central Research and Development (R&D) approvals; months 1-6: set up office, assemble team, and establish first 5 centres; months 7-16: aim to establish trial in all centres; months 7-51: identify and recruit 360 participants; months

13-75: follow up at 6, 12, and 24 months after surgery; months 76-77: final reminders; months 76-82: complete data collection, analysis and dissemination.

The trial will continue to 31 May 2020 with the possibility of longer-term follow-up through a separate funding application.

Milestones for the qualitative component are described in Appendix 2.

|                     |                                                                                                                                                                                                          |
|---------------------|----------------------------------------------------------------------------------------------------------------------------------------------------------------------------------------------------------|
| Before Start | Agree surgical protocols and standardisation of surgical procedures by consensus between grant applicants.
NRES approval                                                                              |
| Year One     |                                                                                                                                                                                                          |
| By month 3          | Set up office and administrative base
Construct customised web-based database, including randomisation program
Establish first five centres (R&D negotiations, appoint local Recruitment Officers) |
| By month 6          | First Trial Steering Committee Meeting
First Data Monitoring Committee meeting
Finalise study documentation, training and teaching materials, questionnaires                                       |
| By month 10         | First Collaborators' Meeting                                                                                                                                                                             |
| Year Two     |                                                                                                                                                                                                          |
| By month 18         | Roll out to other centres (R&D, appoint local Recruitment Officers)
Second Data Monitoring Committee meeting
Second Steering Committee meeting                                                     |
| Year Three   |                                                                                                                                                                                                          |
| By month 30         | Third Data Monitoring Committee meeting
Third Steering Committee meeting                                                                                                                              |
| Year Four    |                                                                                                                                                                                                          |
| By month 42         | Fourth Data Monitoring Committee meeting
Fourth Steering Committee meeting                                                                                                                            |
| Year Five    | Fifth Data Monitoring Committee meeting
Fifth Steering Committee meeting                                                                                                                              |
| Year Six     | Data Monitoring Committee meeting
Steering Committee meeting
Data analysis complete                                                                                                                |
| Year Seven   | Final Steering Committee meeting                                                                                                                                                                         |
| By month 82         | Data archiving, arrangements for long term follow up
Final Collaborators' Meeting                                                                                                                     |

## 8 ORGANISATION

A detailed plan and timetable of study organisation is given in the Gantt chart (Figure 2).

The Gantt chart indicates when it is anticipated that the major study events will occur, including recruitment, trial progress and meetings. There will be approximately three-monthly project management group meetings, six meetings of the Steering Committee and four of the Data Monitoring Committee. Two meetings are planned for collaborators (including urologists, local Research Nurses and consumer participants), the first timed to occur when all the sites have been identified and the second when results are available. There will also be a Training Meeting for the recruitment nurses.

These time-related milestones will be used to enable close monitoring of progress.

### 8.1 Local organisation in centres

#### i) Lead Urologist (Local Principal Investigator)

Each collaborating centre will identify a Lead Urologist who will be the point of contact for that centre.

The responsibilities of this person will be to:

- establish the study locally (for example, by getting agreement from clinical colleagues; facilitate local regulatory approvals; identify, appoint and train a local Research Nurse; and inform all relevant local staff about the study (e.g. other consultant urologists, junior medical staff, secretaries, ward staff)
- take responsibility for clinical aspects of the study locally (for example if any particular concerns occur)
- identify patients who are eligible to participate in the trial, explain the different surgery options to them, and ensure that study documentation has been provided and that informed consent has been obtained
- notify the Study Office of any unexpected, serious clinical events which might be related to trial participation and assess the implications of events leading to these for the safety of other trial participants
- provide support, training and supervision for the local Research Nurse(s)
- represent the centre at the collaborators' meetings

#### ii) Local Research Nurse

Each collaborating centre will appoint a local Research Nurse to organise the day to day recruitment of participants to the trial.

The responsibilities of this person will be to:

- keep regular contact with the local Lead Urologist, with notification of any problem or unexpected development
- maintain regular contact with the MASTER Study Office
- keep local staff informed of progress in the trial
- contact potential participants by: providing the PIL to patients being admitted electively for UI surgery; identifying any eligible patients at pre-assessment clinics or on the ward while they are in hospital for their surgery; explain the study and the potential for participation in a trial if they are eligible; explaining what is intended by research access to their NHS data; and describing the possibility of long-term follow up and participation in other research
- obtain the patient's written consent
- keep a log of whether eligible people are recruited or not (with reasons for non-participation)

- collect baseline data describing the participants, log this information in the web-based MASTER database and send paper copies to the Study Office along with the original signed consent forms in a timely manner
- use this information to randomise the participants using the web-based MASTER database or telephone
- ensure operative and postoperative data (including 12 month clinic CRF hospital readmission form, , withdrawal form and SAE form) are collected and recorded in the web-based MASTER database, and send paper copies to the Study Office in a timely manner
- file relevant study documentation (e.g. consent forms) in the participant's medical records
- organise and supervise alternative recruiters in case of holiday or absence
- represent the centre at the collaborators' meetings

## **8.2 Study co-ordination in Aberdeen**

### **i) The Study Office Team**

The Study Office is in CHaRT, Health Services Research Unit in Aberdeen and provides day to day support for the clinical centres. It is responsible for all data collection (such as mailing questionnaires), follow-up, data processing and analysis. It is also responsible for providing and maintaining the randomisation service, and communicating with the sites about MASTER specific issues. We will produce a yearly MASTER Newsletter for participants and in addition, regular meetings with research nurses and local collaborators to inform everyone of progress and maintain enthusiasm.

The MASTER Study Office Team (Aberdeen-based grant holders and study office members, plus CI) will meet formally approximately monthly during the course of the study to ensure smooth running and trouble-shooting.

### **ii) The Project Management Group (PMG)**

The study is supervised by its Project Management Group. This consists of the grant holders and representatives from the Study Office. Observers may be invited to attend at the discretion of the Project Management Group. They plan to meet or hold a teleconference every three months on average.

### **iii) The Trial Steering Committee (TSC)**

The study is overseen by an independent Trial Steering Committee (TSC). The membership comprises the four independent members (including the Chairman), and the CI (or a deputy). The other grant holders, a representative from the sponsoring institution and the funders (the HTA) may also attend, as may other members of the MASTER Study Office or members of other professional bodies at the invitation of the Chair.

## **8.3 Research Governance, Data Protection and Sponsorship**

### **8.3.1 Research Governance**

The trial will be run under the auspices of CHaRT based at the Health Services Research Unit, University of Aberdeen. This will ensure compliance with Research Governance, and provide centralised trial administration, database support and economic and statistical analyses. CHaRT is a registered Clinical Trials Unit with particular expertise in running multicentre RCTs of complex and surgical interventions.

The CI will ensure, through the TSC that adequate systems are in place for monitoring the quality of the study (compliance with good clinical practise [GCP]) and appropriate expedited and routine reports of adverse effects, to a level appropriate to the risk assessment of the study.

### **8.3.2 Data Protection**

The trial will comply with the Data Protection Act 1998 and regular checks and monitoring are in place to ensure compliance. Data are stored securely in accordance with the Act and archived to a secure data storage facility. The consent form will state that other researchers may wish to access (anonymised) data in the future. The Senior IT Manager (in collaboration with the Chief Investigator) will manage access rights to the data set. Prospective new users must demonstrate compliance with legal, data protection and ethical guidelines before any data are released. It is anticipated that anonymised trial data will be shared with other researchers to enable international prospective meta-analyses.

### **8.3.3 Sponsorship**

The study is sponsored by the North Bristol NHS Trust.

### **8.3.4 Retention of data**

It is intended to follow up the whole cohort of participants for at least 10 years, and data will be retained as long as necessary for this purpose. Permissions will be sought from the relevant Research Governance bodies and the Ethics Committee.

## **8.4 Data and safety monitoring**

### **8.4.1 Data Monitoring Committee**

There is a separate and independent Data Monitoring Committee (DMC). It is anticipated the members will meet once to agree terms of reference and on at least three further occasions to monitor accumulating data and oversee safety issues. This Committee is independent of the study organisers and the TSC. During the period of recruitment to the study, interim analyses will be supplied, in strict confidence, to the DMC, together with any other analyses that the committee may request. This may include analyses of data from other comparable trials. In the light of these interim analyses, the DMC will advise the Steering Committee if, in its view:

- a) one of the methods of surgery has been proved, beyond reasonable doubt\*, to be different from the control (standard management) for all or some types of participants (in respect of either effectiveness or unacceptable safety concerns), and
- b) the evidence on the economic outcomes is sufficient to guide a decision from health care providers regarding recommendation of which operation to choose.

The TSC can then decide whether or not to modify intake to the trial. Unless this happens, however, the TSC, PMG, clinical collaborators and study office staff (except those who supply the confidential analyses) will remain ignorant of the interim results.

The frequency of interim analyses will depend on the judgement of the Chairman of the DMC. However, we anticipate that there might be two interim analyses and one final analysis.

The Chairman and the other independent members are appointed after confirmation by the HTA.

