#### *Expected adverse events*

In this study the following adverse events are potentially expected:

- Possible (expected) adverse events during or associated with surgery include:
  - excess blood loss (>500 ml) or transfusion;
  - injury to organs (eg bladder, bowel, urethra), blood vessels or nerves
  - anaesthetic complications;
  - death
- Possible (expected) adverse events following surgery include:
  - excess blood loss (>500 ml);
  - blood transfusion;
  - haematoma;
  - prolongation of post-operative catheterisation;
  - recatheterisation;
  - urinary retention/voiding difficulties requiring surgical intervention; urinary retention/voiding difficulties not requiring catheterisation or surgery;
  - bowel obstruction;
  - constipation;
  - thrombosis/DVT/pulmonary embolism;
  - urinary tract infection;
  - wound infection;
  - wound breakdown
  - other infection (sepsis, septicaemia, abscess);
  - new bothersome urinary tract symptoms;
  - division of male sling;
  - device exposure/extrusion which requires no treatment or conservative treatment;

- device exposure/extrusion requiring hospitalisation for surgical removal of the device;
- abnormal pain (acute or chronic e.g. /buttock or groin pain/sciatica);
- new bothersome sexual problems;
- death

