##### *Reporting responsibilities of the CI*

When the SAE form is uploaded onto the trial website, the CI or Trial Manager will be automatically notified. If, in the opinion of the local Principal Investigator (PI) and the CI, the event is confirmed as being *serious* and *related* and *unexpected*, the CI or Trial Manager will notify the sponsor within 24 hours of receiving the SAE notification. The CI or Trial Manager will notify the sponsor of expected SAEs in a timely fashion. The sponsor will provide an assessment of the SAE. The CI (or Trial Manager) will report any related and unexpected SAEs to the main Research Ethics Committee (REC) and the DMC within 15 days of the CI becoming aware of it. All related SAEs will be summarised and reported to the Ethics Committee, the Funder and the Trial Steering Committee in their regular progress reports.

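### Section 8.4.1 as worded ties DMC advice on safety to sufficient economic evidence, and Section 8.4.3 lists death as expected, which takes a surgery-related death outside the fixed reporting deadlines

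*Protocol*

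**What the plan says.** **DMC advice (Protocol 8.4.1).** On seeing interim analyses, "the DMC will advise the Steering Committee if, in its view", two lettered conditions apply. Condition a) is that one operation has been shown beyond reasonable doubt to differ, "in respect of either effectiveness or unacceptable safety concerns), and". Condition b) is that "the evidence on the economic outcomes is sufficient to guide a decision from health care providers". The TSC may then decide whether to change intake. Unless this happens, the TSC, the management group, the collaborators and most study office staff "will remain ignorant of the interim results". The same section gives the DMC the task "to monitor accumulating data and oversee safety issues".

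**Deaths (Protocol 8.4.3 and 8.4.4).** A fatal event is serious by definition. Two lists of expected events follow, one for surgery itself and one introduced by "Possible (expected) adverse events following surgery include". Death is an unqualified entry in both. Under the CI's reporting responsibilities, the sponsor is told within 24 hours of events confirmed as serious, related and unexpected. For the other bodies, "The CI (or Trial Manager) will report any related and unexpected SAEs to the main Research Ethics Committee (REC) and the DMC within 15 days". For the rest, "The CI or Trial Manager will notify the sponsor of expected SAEs in a timely fashion". Related serious adverse events (SAEs) are also summarised in regular progress reports to the Ethics Committee, the Funder and the TSC.

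**The concern.** Safety appears in Section 8.4.1 only as one branch of condition a), and condition a) is joined to the economic condition. A DMC that saw unacceptable harm with one device, but immature cost data, would find no sentence providing for advice to the TSC on that ground alone. The next sentences add to the difficulty, because they keep the TSC blind to interim results unless the stated conditions have arisen.

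In Sections 8.4.3 and 8.4.4 the difficulty is classification. Fixed deadlines apply only to unexpected events, and death is on the expected lists. The most serious outcome of a continence operation would then carry no set deadline, and the DMC is not named among the recipients of the progress reports.

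At stake is whether the independent monitors can act on safety alone, and whether they learn promptly of a death caused by trial surgery. Both rules are fixed in the protocol, so neither point is one normally left to a statistical analysis plan.

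**Working it through.** The protocol states no figure to reproduce here. The check is the logic of the text plus simple calendar arithmetic.

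**1. Logical form of the DMC rule.** Taking the conjunction at face value:

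advice = (effectiveness OR safety) AND economics

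| Effectiveness difference | Unacceptable safety | Economics sufficient | Condition for advice met |
|---|---|---|---|
| no | yes | no | **no** |
| no | yes | yes | yes |
| yes | no | no | no |
| yes | no | yes | yes |

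The first row is the problem: safety alone does not satisfy the rule.

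**2. When economic evidence becomes available.** Inputs: recruitment in months 7 to 51 (Section 7); primary economic outcome is cost per QALY at 24 months (Sections 2 and 5.1.1); EQ-5D and resource-use questionnaires at 6, 12 and 24 months (Table 1). Counting from randomisation:

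- First 6-month data: 7 + 6 = month 13.
- First 12-month data: 7 + 12 = month 19.
- First 24-month data: 7 + 24 = month 31.
- Last 24-month data: 51 + 24 = month 75.
- Men with 24-month data when recruitment closes: those randomised by 51 − 24 = month 27.

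Months 13 and 75 agree with the follow-up window given in Section 7. If follow-up is counted from surgery, as Section 7 has it, each date moves later by the wait for surgery.

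So for 31 − 7 = 24 of the 51 − 7 = 44 months of recruitment there are no 24-month economic data. For the remaining 51 − 31 = 20 months there are some. Condition b) does not name the 24-month outcome, and it is judged in the DMC's view, so earlier data could also count. The condition is hard to meet early, but not impossible.

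**3. A surgery-related death traced through Section 8.4.**

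| Step | Source | Result |
|---|---|---|
| Serious? | 8.4.3 definitions | yes |
| Related? | 8.4.3 definitions | yes, by the premise |
| Expected? | 8.4.3 lists | yes; death is in both |
| Recorded on the SAE form? | 8.4.4 Recording | yes; all deaths of any cause |
| CI or Trial Manager alerted? | 8.4.4 Reporting | yes, automatically on upload |
| 24-hour notice to sponsor? | 8.4.4 Reporting | no; requires unexpected |
| 15-day report to REC and DMC? | 8.4.4 Reporting | no; requires unexpected |
| Sponsor told by another route? | 8.4.4 Reporting | yes, with no set limit |
| Progress reports? | 8.4.4 Reporting | yes, to the Ethics Committee, Funder and TSC; DMC not named |

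The DMC's remaining scheduled view is its own review of accumulating data, which Section 6.1.2 sets at no less than once a year. On the text alone, the wait could approach a year.

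**The case against.** **The DMC rule says when advice will be given, not that it is otherwise forbidden.** This stands. A reader might infer that the DMC may advise on safety only if the economic condition is met. The word only is not in the text, and the conjunction may be a loose link between two list items. The DMC has a general safety role and may ask for any analysis. Section 8.4.2 sends concerns about procedures and participants to its Chairman. An economic precondition for safety was probably not intended. But these provisions bring information to the DMC; none writes a route from safety alone to advice. The inconsistency between the rule and the safety role remains.

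**The economic condition can be met while recruitment is open.** This also stands. A reader might infer that no safety signal during recruitment could ever lead to advice. The dates above do not support that: 6- and 12-month data come earlier, and 24-month data accrue from about month 31.

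**Expectedness is judged case by case, and deaths are not hidden.** Largely right. The local investigator and the CI give the opinion on whether an event is unexpected, the lists are introduced as potential events, the sponsor assesses each SAE, and Section 8.4.2 says the relevant reporting guidelines will be followed. A reader might infer that related deaths go unreported; the protocol does not say that. What remains is that an assessor who follows the list will class a death as expected, and neither deadline then applies.

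**Two further inferences should not be drawn.** The footnote on three standard deviations says such a difference may be needed for a major endpoint and that exact criteria cannot be given; it sets no safety threshold. The reference to standard management as control is not a fault either, since Section 3.4 names the artificial urinary sphincter as the standard technique.

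**Conclusion.** Both points hold as defects of wording. Section 8.4.1 provides for advice on (effectiveness or safety) together with economics and writes no safety-only route, in tension with the DMC's own safety role. Sections 8.4.3 and 8.4.4 together place a surgery-related death outside the two fixed deadlines and leave the DMC without fixed-time notice of it.

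The size is limited. The economic condition is a weak basis for advice over roughly the first 24 of 44 recruitment months, not a complete bar. The gap for deaths concerns the 24-hour and 15-day deadlines, not recording or eventual reporting.

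The conclusion assumes that the conjunction is read literally, that the unqualified entries for death guide the judgement of expectedness, and that nothing in the DMC's terms of reference, which are not shown, overrides the protocol. Even if the terms of reference are clearer, the protocol should agree with them.

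**What to change.** - **Section 8.4.1:** state that unacceptable safety concerns alone, in the DMC's judgement, are grounds to advise the TSC, and that condition b) applies only to effectiveness. Align the DMC's terms of reference.
- **Sections 8.4.3 and 8.4.4:** reconcile them, either by removing death from both expected lists or by stating that any related death follows the 24-hour and 15-day route whatever its expectedness. Either change gives the DMC fixed-time notice.

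The cost is a protocol wording amendment and, at most, a few more expedited reports. Sample size, data collection and analysis are unaffected.
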